## Abstract

**Background:**

The 'Healthy Dads, Healthy Kids' program was designed to help overweight fathers lose weight and positively influence the health behaviors of their children. The aim of the current study was to evaluate the previously established program in a community setting, in a large effectiveness trial.

**Methods/Design:**

The Healthy Dads, Healthy Kids community trial consists of three stages: (i) *Stage 1 - program refinement and resource development *(ii) *Stage 2 - community randomized controlled trial *(iii) *Stage 3 - community effectiveness trial*. The program will be evaluated in five Local Government Areas in the Hunter Valley Region of NSW, Australia. For the community randomized controlled trial, 50 overweight/obese men (aged 18-65 years) from one Local Government Area with a child aged between 5-12 years of age will be recruited. Families will be randomized to either the program or a 6-month wait-list control group. Fathers and their children will be assessed at baseline, post-intervention (3-months) and 6-months. Inclusion criteria are: body mass index 25-40 kg/m^2^; no participation in other weight loss programs during the study; pass a health-screening questionnaire; and access to a computer with Internet facilities. In the community trial, the program will be evaluated using a non-randomized, prospective design in five Local Government Areas. The exclusion criteria is body mass index < 25 kg/m^2 ^or lack of doctor's approval. Measures will be collected at baseline, 3-, 6- and 12-months. The program involves fathers attending seven face-to-face group sessions (three with children) over 3-months. *Measures*: The primary outcome is fathers' weight. Secondary outcomes for both fathers and children include: waist circumference, blood pressure, resting heart rate, physical activity, sedentary behaviors and dietary intake. Father-only measures include portion size, alcohol consumption, parenting for physical activity and nutrition and parental engagement. Process evaluation will determine the fidelity, dose (delivered and received), reach, recruitment and context of the program.

**Discussion:**

As a unique approach to reducing obesity prevalence in men and improving lifestyle behaviours in children, our findings will provide important evidence relating to the translation of Healthy Dads, Healthy Kids, which will enable it to be delivered on a larger scale.

**Trial registration:**

Australia and New Zealand Clinical Trials Register (ANZCTR): ACTRN12610000608066

## Background

Obesity is a serious public health concern associated with numerous negative health consequences [1]. Its prevalence is high and increasing [2], especially among men [3]. This is concerning given that men are less likely to self-identify as being overweight [4], attempt weight loss, or enroll in weight loss programs compared to women [5,6]. Although this is a concern, perhaps of greater worry is the impact obese fathers may have on their children. A recent study demonstrated that a father's parenting style was more influential than a mother's parenting style on their pre-school child's weight status [7]. Fathers' dietary intake has also been shown to be associated with their children's dietary intake [8]. Notably, a longitudinal study of more than 3200 families identified that having an overweight or obese father, but a healthy weight mother, increased the odds of a child becoming obese [9]. However, the reverse scenario (having an overweight mother with a healthy weight father) was not a significant predictor of childhood obesity. These findings provide emerging evidence that fathers are a key influence in shaping the home environment that may influence children's dietary and physical activity behaviors.

As parent behaviors, attitudes, parenting styles and practices have a profound influence on children's health behaviors [10,11], there is an urgent need to explore the feasibility and efficacy of lifestyle interventions that target parents and aim to influence the health behaviors of both parents and children. Despite the widely accepted notion that physical activity and dietary interventions for children should involve parents, the most appropriate strategies to recruit, engage and improve parental lifestyle behaviors have not been established [12,13]. Further, family-based lifestyle interventions have mainly engaged mothers [12]. We conducted the only experimental study targeting fathers, the *Healthy Dads, Healthy Kids *(HDHK) pilot, which examined the impact of a lifestyle program targeting fathers on children's physical activity and dietary habits [14].

The HDHK program was designed to help overweight fathers lose weight and role model positive health behaviors in order to positively influence the physical activity and dietary behaviors of their children. Preliminary studies have shown the program to be highly feasible and efficacious [14], with approximately 85% of fathers achieving a clinically important [15] weight loss (≥ 5% of their starting weight). In addition, children in the HDHK group significantly improved their physical activity levels and decreased their kilojoule intake, relative to those in the control group. The process evaluation also highlighted the feasibility of this approach with high levels of recruitment, retention, attendance and satisfaction of participants [14].

Despite the results of the HDHK pilot study, efficacy was established in a university-based research project that was delivered by highly qualified staff in a closely monitored trial. While efficacy is an essential first step and evaluates outcomes under ideal conditions, effectiveness measures the impact of an intervention when implemented in a real-world setting and represents a more realistic evaluation of the likely intervention effect [16]. While efficacy is more associated with internal validity, effectiveness relates more to external validity and examines whether an intervention can be translated to a real-world setting [16].

Therefore, the generalizability and effectiveness of the HDHK program requires testing in an appropriate trial to determine the impact of the program when delivered by trained community-based facilitators and with longer-term follow-up. This type of translational research will maximize the public health impact and reach of the HDHK program. There is an urgent need to translate obesity prevention and treatment programs with demonstrated efficacy into real-world settings [17] to reduce the significant void between research and practice and between the efforts of policy makers, researchers and practitioners in this field [18]. The aim of the current study is to implement and evaluate the HDHK program in an effectiveness trial set in the community.

## Methods/Design

### Study Design

The HDHK community trial consists of 3 major stages:

Stage 1 - Program refinement and resource development

Stage 2 - Community randomized controlled trial (RCT)

Stage 3 - Community effectiveness trial

The HDHK community program will be evaluated in five Local Government Areas (LGAs; Singleton, Maitland, Scone, Muswellbrook, Cessnock) in the Hunter Valley Region of New South Wales, Australia. In these areas, there are high levels of employment within the mining and associated manufacturing industries. In Australia, 52% of men who work in the mining industry are engaged in shift work [19], which is associated with increased health issues compared with working daytime hours and is an independent predictor of increased body mass index [20].

Stage 1 - Program refinement and resource development (2010)

One local government area (Singleton) was targeted in order to develop and test strategies for engaging communities, promoting the program among residents, and recruiting participants. Stage 1 was also used to further refine and develop key resources for families and for facilitators. For example, the session content was extensively reviewed and updated and more participant-centered learning experiences were embedded throughout the program. These developments were informed by the process evaluation of the pilot study [21] and from participant and facilitator feedback after running the HDHK program with a small group of fathers (n = 6) and their children from a primary school in Singleton in 2010. This trial of the HDHK program was delivered by [name] and the sessions were filmed to (a) assist with development of the training manual, and (b) be used as a facilitator training resource to demonstrate interactions with fathers that occur when implementing the program and visual demonstrations of the practical activities used in the interactive nights for fathers and their children. Details of the resources developed for the HDHK program are outlined in Table 1.

**Table 1 T1:** HDHK program resources

Resource	Brief description	Included information
Facilitator manual	Comprehensive train-the-trainer manual detailing all information required for the delivery of the program	* Introduction * Successful facilitating * Background to the research * Session guides

Manual for Dads	Handbook for fathers that includes a summary of the information from the face-to-face sessions and additional background information	* Session 1: Weight loss fundamentals for men * Session 2: Raising children in an inactive world * Session 3: Ready to rumble with dad * Session 4: Healthy eating for families - dads matter * Session 5: Fun, fitness and fundamental movement skills * Session 6: Sustaining healthy lifestyles * Session 7: Weight loss is a journey not a destination

Dad's log book	Handbook that dads use as a working document	* Program activities: Energy calculations; sedentary behaviors; goal setting; eating habits * Homework activities: Children's screen time; family fitness activity; family cooking; children's food intake; cue words; family activity * Monitoring procedures: Pedometer chart; weight loss chart; goal recording

Website user guide	Handbook to guide fathers through the setup and use of the dietary and physical activity monitoring website	* Setting up a profile * Food and exercise diary * Check in diary * Charts and reports

Kid's Handbook	Includes tasks for children to complete each week with their dads that must be signed off with their dads (space to receive a sticker from facilitators if completed)	* Kids homework activities * Recipes to cook with dad

Green slips	Homework activity slips given to fathers at the end of each session	* Activities are designed to align with the principles presented at the intervention session and any activities detailed in the Dad's log book and Kid's handbook (e.g. cooking meals with kids, family fundamental movement skills circuit, rough and tumble games with dad)

Stage 2 - Community RCT design

With the facilitator training and resources developed, the impact of the program in a community setting will be evaluated with trained local facilitators, employing a RCT design.

#### Participants

Overweight or obese (BMI between 25 and 40 kg/m^2^) fathers (aged 18-65 years) with a child aged between 5 and 12 years of age (i.e. primary school age) will be recruited from the local communities using the following strategies: local media releases (print, TV and radio), school newsletters items, school-based presentations, fliers distributed through community notice boards and local businesses, paid advertisements in local newspapers, local networks of sports clubs, service clubs, local government, and community health facilities. Fathers will be screened for eligibility via telephone. Ethics approval has been obtained from the University of Newcastle Human Research Ethics Committee. Written informed consent will be obtained from the fathers prior to their participation as well as child assent.

Fifty fathers will be recruited from one LGA (Maitland) and randomized to either the HDHK program or a 6-month wait-list control group. Fathers (and their children) will be stratified by BMI category (overweight [25-29.9 kg/m^2^], obese class 1 [30-34.9 kg/m^2^], obese class 2 [35-40 kg/m^2^]) and randomized using a computer-based random number-producing algorithm, to intervention or control group. To ensure concealment, the sequence will be generated by a statistician and given to the project manager. Randomization will be completed by a research assistant not involved in assessments and the allocation sequence will be concealed when enrolling participants. Fathers and their children will be assessed at baseline, post-intervention (3-months) and 6-months (3-months post-intervention).

#### Inclusion/exclusion criteria

Ineligibility criterions consist of a history of major medical problems such as heart disease in the last five years, Type 1 diabetes, orthopedic or joint problems that would be a barrier to physical activity, recent weight loss of ≥ 4.5 kg and taking medications that might affect body weight. All fathers need to have a BMI between 25 and 40, have internet access and will be asked to not participate in other weight loss programs during the study. Fathers will complete a pre-exercise risk assessment screening questionnaire [22]. Any participant over the age of 40 will be required to provide a doctor's clearance before enrolling in the study.

#### Sample size

For the RCT, based on 80% power to detect a significant weight loss difference between groups of 3 kg, assuming SD = 5 (*P *= 0.05, two-sided) a sample size of 20 fathers for each group will be needed at 6 months. Assuming a 20% attrition rate [14], a total sample of 50 fathers will be required. Participants will be blind to group allocation at baseline assessment. Once baseline assessments are completed, participants will receive a sealed envelope with a note advising their group allocation. The wait-list control group will receive no information or intervention before attending the 3- and 6-month follow-up assessment sessions. There will be a 6-month wait-list control group as (a) ethically every overweight man is deserving of an intervention and is unlikely to remain weight stable; (b) randomization to 'no' intervention for a greater length of time is unlikely to be acceptable and is likely to lead to high attrition compromising study integrity.

Stage 3 - Community effectiveness trial design

When translating evidence-based programs into real-world settings, ongoing modifications are required based on the unique characteristics of the settings and populations. Modifications will be made to the program based on both outcome and process evaluation from the community RCT and each subsequent program implementation in 2011 and these will be documented. The goal will be to develop a comprehensive model of a real-world intervention for application in communities through updating materials, developing standardized train-the-trainer education and resources and ongoing evaluation of the implementation of the intervention with a final evaluation conducted in 2012.

The HDHK program will be evaluated for effectiveness in the community roll-out using a non-randomized, prospective design. This evaluation will be conducted in both 2011 and 2012 in the five local government areas. The exclusion criteria is minimal to align with a true translational model and will only include BMI < 25 or lack of doctor's approval. Measures (detailed below) will be collected at baseline, post-intervention, and 6 and 12 months post-baseline. We aim to recruit 15-20 fathers from each area. Results from each program will be pooled and it is expected at least 200 families will participate in the community trial of the HDHK program.

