#### Primary outcome measure

The primary outcome measure is body weight of the fathers at 6-month follow-up. Weight will be measured with fathers wearing light clothing, without shoes on a digital scale to 0.1 kg (model CH-150 kp, A&D Mercury Pty Ltd, Australia). Weight will be recorded twice and the average of the two measures reported. The same protocol will be followed to record children's weight.

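### On the stated inputs, 20 fathers per group give about 46% power for a 3 kg difference, not 80%; 44 to 45 per group would be needed

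*Protocol article*

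**What the plan says.** The protocol article's Sample size section gives all the inputs of the calculation in one sentence: "based on 80% power to detect a significant weight loss difference between groups of 3 kg, assuming SD = 5", with a two-sided significance level of 0.05. From these it concludes that "a sample size of 20 fathers for each group will be needed at 6 months". It then allows for 20% attrition and states that "a total sample of 50 fathers will be required".

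The calculation serves the primary endpoint of the randomised stage: "The primary outcome measure is body weight of the fathers at 6-month follow-up" (Primary outcome measure). The Data Analysis section plans a mixed model with group, time and their interaction, fitted to all randomised participants. Neither section gives a baseline-to-follow-up correlation, a covariate adjustment or a repeated-measures gain that entered the sample size.

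**The concern.** A 3 kg difference with SD 5 is a standardised effect of 0.6. Twenty per group is well short of what an effect of that size needs for 80% power in a two-sided comparison of two groups. The gap is too large to be rounding or a difference between software packages.

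This is the only power justification for the primary outcome in the only randomised stage. If the true benefit is 3 kg, the trial at its planned number of completers is slightly more likely to miss it than to find it. A reader who trusts the stated 80% could then take a non-significant result as evidence that the community version does not work. The same section says that outcome results from the randomised stage will inform changes to the program before and during the community roll-out, so a misread null result could affect later decisions.

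**Working it through.** **Inputs, all from the Sample size section.** Difference δ = 3 kg; SD σ = 5 kg, attached to weight loss and so read as the SD of change; two-sided α = 0.05; power 80%; equal groups; 20 per group at 6 months; 20% attrition; total 50.

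**1. Trying to reproduce 20 per group.**

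n per group = 2(z₀.₉₇₅ + z₀.₈₀)²σ²/δ² = 2 × (1.96 + 0.842)² × 25/9 = 43.6, so 44. With the noncentral t distribution it is 44.6, so 45. The stated 20 is not reproduced.

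**2. Power at the stated size.**

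| Completers per group | Normal approximation | t test |
|---|---|---|
| 20 | 47.5% | 45.6% |
| 25 (no attrition) | 56.4% | 54.7% |

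**3. What 20 per group does support (t test).**

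- The standardised effect detectable with 80% power is 0.909, so the detectable difference at SD 5 is 0.909 × 5 = 4.55 kg (4.43 kg by the normal approximation).
- For 3 kg to be detectable, the SD would have to be 3/0.909 = 3.30 kg (3.39 kg by the normal approximation).
- Expected 95% CI half-width: t₃₈ × 5 × √(2/20) = 2.024 × 1.581 = 3.20 kg.

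**4. The attrition step.** 40/(1 − 0.2) = 50, as stated. The same step on the recomputed size gives 88/0.8 = 110 or 90/0.8 = 112.5, so 113 (114 for two equal groups of 57).

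**5. Could another method give 20?**

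- *One-sided 5%:* 35 (normal) or 36 (t) per group. The text says two-sided.
- *One-sample formula, without the factor 2:* 21.8, so 22 (normal), or 23.8, so 24 (t), two-sided. A one-sided one-sample t test gives 18.6, so 19. These come close to 20, and an omitted factor of 2 is a possible origin, but none is valid for a two-sided comparison between groups.
- *Baseline adjustment with SD 5 as the SD of weight itself:* n = 20 needs a baseline-to-6-month correlation of about 0.75 (ANCOVA, t test; 0.74 normal) or about 0.78 (change score). Over an assumed range of correlations, ANCOVA by the normal approximation needs 33 per group at 0.5, 23 at 0.7 and 16 at 0.8. No correlation is stated, and the sentence ties SD 5 to weight loss. A 5 kg SD of body weight is also not credible here: eligible BMI runs from 25 to 40, and at an assumed height of 1.70 to 1.85 m that is 15 × 1.70² = 43 kg to 15 × 1.85² = 51 kg of body weight. A single 5-unit BMI stratum spans about 14 to 17 kg.
- *Baseline adjustment with SD 5 as the SD of change:* the residual SD is 5√((1 + ρ)/2), where ρ = 1 − 25/(2 × SD²) and SD is that of body weight. For an assumed weight SD of 10, 15 or 20 kg, ρ is 0.875, 0.944 or 0.969 and the residual SD is 4.84, 4.93 or 4.96 kg. At 4.84 kg, the most favourable of these, n = 15.7 × 4.84²/9 = 40.9, so still 41 per group.

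**The case against.** The arithmetic is hard to dispute; what can be contested is how much to read into it.

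- *Which number is wrong?* The document cannot show this. The sample size, SD, difference and power are mutually inconsistent, and the slip could lie in any of them; an SD of about 3.3 kg would reconcile the rest. This stands. The finding is that the four figures cannot all be true together, not that 20 was necessarily the mistyped one.
- *Is the trial more likely to miss a 3 kg effect than find it?* Only at the planned 20 completers. The mixed model keeps partial data from dropouts, so the effective size may lie between 20 and 25, and power passes 50% at about 22.5 per group. A fair range is 46% to 55%. This stands too, but the whole range is far below 80%.
- *Is the real effect larger?* The Background reports that about 85% of pilot fathers lost at least 5% of starting weight. For assumed starting weights of 80 to 125 kg, 5% is about 4 to 6 kg, and 20 per group with SD 5 would have 69% power for 4 kg, 87% for 5 kg and 96% for 6 kg. This mitigates only partly: the pilot figure is not a between-group difference, the Background itself warns that results under ideal conditions may not carry over to the community, and the stated target is 3 kg.
- *Would a null result really be misread?* That is a risk rather than a certainty. The Data Analysis section already plans mean differences with 95% confidence intervals, and the roll-out does not depend on significance in the randomised stage.

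None of this makes the sentence in the Sample size section correct.

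**Conclusion.** The concern holds, and the sample size statement must be corrected. With the stated inputs, 80% power needs 44 to 45 fathers per group at 6 months, more than twice the 20 claimed. At 20 per group the power is about 46%, roughly 34 percentage points below the claim; full retention of 25 per group would raise it only to about 55%.

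This rests on reading SD 5 as the common SD of weight loss in a two-sided comparison of two equal groups, which is what the sentence says. The only alternatives that reach 20 need an SD or a correlation that the document does not state, or a formula that does not fit the design. The article does not leave the calculation to a fuller document: it prints both the inputs and a result that contradicts them.

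**What to change.** Correct the Sample size section. The least disruptive option keeps 50 fathers and changes the claim: with 20 completers per group and an SD of 5 kg, the trial has 80% power for a difference of about 4.55 kg and about 46% power for 3 kg.

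Other routes are open to the sponsor:

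- If a smaller SD was intended, state and justify it (about 3.3 kg is needed for 3 kg with 20 per group).
- If a gain from baseline adjustment was intended, state the correlation and say which SD it applies to.
- If 80% power for 3 kg at SD 5 is essential, raise the number randomised to about 110 to 114.

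In any case, add a sentence saying that a non-significant result will be interpreted by whether its 95% confidence interval excludes a 3 kg benefit.

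The first option is a text correction with no extra recruitment; its price is a less favourable power statement. Only the third changes the size of the trial.

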### The HDHK Intervention

The aims of the program are to help fathers achieve their weight loss goals, become healthy role models, and promote healthy behaviors for their children. Table 2 details the specific HDHK program content for each session. The 3-month HDHK program involves fathers attending seven face-to-face group sessions (90 minutes each). Four group sessions are for fathers only, and three sessions involve both the fathers and their children. These practical sessions will be conducted in local school halls and delivered by two trained facilitators.

**Table 2 T2:** HDHK sessions and program content

Session focus	Session detail
1. 'Weight loss for men' (Dads)	* Program rationale * Importance of fathers and their influence on children * Energy balance and weight loss * Nine key weight loss tips for men * Website use for eating and activity diaries

2. 'Raising active children in an inactive world' (Dads)	* Obesogenic environments * Physical activity levels, trends and benefits * Physical activity recommendations * Physical activity goals for Dads * Ideas for fitness/activity at home

3. 'Ready to rumble with Dad' (Dads & Kids)	* Rough and Tumble Play * Fun Fitness circuits * Fun and active games

4. 'Healthy eating for families - Dads matter' (Dads)	* Healthy eating benefits * Child nutrition * Food based guidelines * Role of fathers in healthy home eating environments * Authoritative feeding practices * Reading food labels

5. 'Fitness, fun and fundamental movement skills (FMS)' (Dads & Kids)	* FMS skills circuit * Rough and Tumble activities * Partner fitness challenges

6. 'Sustaining healthy lifestyles' (Dads)	* Planning meals * Australian Guide to Healthy Eating * Recommended daily intakes * Why we eat food? * Support and strategies for successful dietary changes and relapse prevention

7. 'Weight control is a journey, not a destination' (Dads & Kids)	* Program revision * Challenges and solutions * Rough and tumble activities * Ball and game skills

The HDHK program is based on Social Cognitive Theory (SCT) [23] and Family Systems Theory (FST) [24]. The following SCT constructs are targeted and operationalized: self-efficacy, goals/intention, outcome expectations, perceived facilitators and barriers to changes, and social support. FST postulates a complex theoretical framework of reciprocal relationships among family members. That is, when a parent changes his or her physical activity and dietary behaviors this will be reflected in the child's behavior [25]. HDHK provides fathers with the knowledge and skills important for long-term behavior change. HDHK teaches fathers about the importance of spending quality time with their children and uses healthy eating and physical activity as the medium to engage fathers with their children. By including the children in the HDHK sessions, children's enthusiasm for father-child activity can reinforce the shift in family lifestyle.

Sessions on healthy eating for families focus on various aspects of parental influence on children's dietary intake incorporating Satter's 'trust' paradigm [26], which suggests parents should supply healthy foods and a supportive eating environment and children can decide when and how much to eat. Sessions focus on promoting a 'do as I do' and not a 'do as I say' philosophy and making small changes, building on initial success and setting up a home environment where sustainable healthy family eating patterns can be established. The physical activity and dietary component focus on an authoritative parenting style to facilitate better dietary and activity choices for children and have been informed by the dietary intervention previously implemented in the successful HIKCUPS child obesity intervention [27,28]. Although mothers do not attend sessions, fathers are encouraged to enhance social support for their child's efforts and consider strategies to involve mothers.

